#### **4.6.1.1 Discontinuation from Study Drug**

All study medications should be stopped for individual patients for any of the following reasons:

- Hepatitis C virus RNA titer > 100 IU/mL by Week 24
- Quantifiable HCV RNA at Week 24
- Hepatitis C virus RNA virologic breakthrough before the end of treatment with boceprevir and/or RO5024048/placebo and/or Pegasys/Copegus. Virologic breakthrough is defined as:

A sustained increase in HCV RNA of  $\geq 1 \log_{10}$  IU/mL ( $\geq 2$  consecutive measurements) while on boceprevir/RO5024048 compared with the on-treatment nadir (where the nadir is a  $\geq 1 \log_{10}$  IU/mL decrease from baseline after 2 weeks of treatment or  $\geq 2 \log_{10}$  IU/mL decrease from baseline after 4 weeks of treatment)

Confirmed quantifiable HCV RNA ( $\geq 25$  IU/mL by  $\geq 2$  consecutive measurements) in a patient who had been previously confirmed as having unquantifiable HCV RNA ( $< 25$  IU/mL by  $\geq 2$  consecutive measurements) before the end of treatment with boceprevir/RO5024048

Response ( $< 25$  IU/mL by  $\geq 2$  consecutive measurements) to boceprevir/RO5024048 treatment and subsequent quantifiable viral load ( $\geq 25$  IU/mL by  $\geq 2$  consecutive measurements) once boceprevir/RO5024048 treatment has been completed (but Pegasys/Copegus treatment continues)

- Hepatitis C virus partial response before the end of treatment with boceprevir/RO5024048/Pegasys/Copegus/placebo, defined as an initial HCV RNA decline ( $\geq 1 \log_{10}$  IU/mL decrease from baseline after 2 weeks of treatment or  $\geq 2 \log_{10}$  IU/mL decrease from baseline after 4 weeks of treatment) followed by stabilization ( $\geq 2$  consecutive measurements similar to those at nadir) while on boceprevir/RO5024048/Pegasys/Copegus/placebo treatment and/or a HCV RNA  $\geq 1000$  IU/mL by the end of boceprevir/RO5024048/Pegasys/Copegus/placebo treatment of at least 4 weeks in duration
- Any confirmed Grade 4 laboratory abnormality deemed clinically significant (based on the investigator's assessment)
- A positive troponin value ( $> 0.100$  ng/mL)

RO5024048 should be stopped for individual patients for any of the following reasons:

- A creatinine clearance decrease  $\geq 35\%$  from baseline or  $< 60$  mL/min ( $< 1.00$  mL/sec) confirmed by repeat test, preferably within 1 week

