- A urine protein/creatinine ratio  $\geq 0.5$  (56.51 mg/mmol) and greater than the baseline value confirmed by repeat test, preferably within 1 week (see [Appendix H](#))

Refer to [Appendix F](#) and [G](#) for more details on stopping rules and for additional guidance on the management of specific AEs and laboratory abnormalities.

Patients who discontinue study drug prematurely will be asked to return to the clinic for a Study Completion/Early Termination Visit (see Section [4.5.2.3](#)) and may undergo follow-up assessments (see Section [4.5.2.4](#)). The primary reason for premature study drug discontinuation should be documented on the appropriate eCRF. Patients who discontinue study drug prematurely will not be replaced.

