#### **RO5024048 AND BOCEPREVIR DOSE INTERRUPTION OR DISCONTINUATION**

No dose modifications will be allowed for RO5024048 or boceprevir.

RO5024048 must be discontinued immediately and the Sponsor's Medical Monitor contacted within 24 hours if any of the following are confirmed and **considered related** to the study drug:

- Creatinine clearance:  $\geq 35\%$  decrease from baseline or  $< 60$  mL/min ( $< 1.00$  mL/sec) confirmed by repeat test, preferably within 1 week
- Any clinically significant Grade 4 laboratory abnormality confirmed by repeat test, preferably within 1 week, unless otherwise defined
- Any SAE assessed as related to RO5024048

It is important that patients receive the full dose of RO5024048 and/or boceprevir. However, moderate or severe adverse reactions (clinical and/or laboratory) may necessitate dose interruption or discontinuation of RO5024048 and/or boceprevir.

If a dose of RO5024048 or boceprevir is missed and the patient remembers the same day, the patient must take the missed dose if the next scheduled dose is more than 4 hours away. The patient should not take two doses at the same time or within 4 hours of each other.

Patients who discontinue all study drugs should return for the PW visit as soon as possible after their last dose of study medication, according to [Appendix A](#). Patients who prematurely discontinue from the study will be assessed for safety and efficacy at 4 and 12 weeks after the last dose of study treatment. In addition, patients who prematurely discontinue and have unquantifiable HCV RNA will be assessed for efficacy at 12 weeks after the last dose of study treatment as long as they remain HCV RNA unquantifiable at their last assessment.

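### Section 4.6.1.1 and Appendix F give different stopping rules for the same Grade 4 laboratory and creatinine clearance triggers, and nothing says which governs

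*Protocol*

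**What the plan says.** Protocol section 4.6.1.1 has two lists. The first opens "All study medications should be stopped for individual patients for any of the following reasons" and includes "Any confirmed Grade 4 laboratory abnormality deemed clinically significant" on the investigator's assessment. The second opens "RO5024048 should be stopped for individual patients for any of the following reasons" and includes "A creatinine clearance decrease" of at least 35% from baseline, or a value below 60 mL/min, confirmed by repeat. Neither item carries a causality condition or an exception. The section then refers sites to Appendices F and G "for more details on stopping rules and for additional guidance on the management of specific AEs and laboratory abnormalities".

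Appendix F, under the heading for RO5024048 and boceprevir interruption or discontinuation, says "RO5024048 must be discontinued immediately", with the Medical Monitor contacted within 24 hours, when a listed event is confirmed and "considered related" to study drug. The list gives the same creatinine clearance thresholds and also "Any clinically significant Grade 4 laboratory abnormality confirmed by repeat test, preferably within 1 week, unless otherwise defined".

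Table F3, part of the Pegasys guidance in Appendix F, says what to do at ANC below 500 cells/mm³ (hold Pegasys until ANC exceeds 750, then restart at 90 µg) and at platelets below 25,000 cells/mm³ (withhold, and monitor at least weekly). In Appendix I those two limits are the adult Grade 4 cut-offs.

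**The concern.** The text that sites are sent to for detail is narrower than the rule it is meant to detail. It covers fewer drugs and adds a causality test. An investigator who takes Appendix F as the operative version has written support for keeping a patient on treatment that 4.6.1.1 ends.

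The renal case matters most. Section 1.2.1 says that the parent drug and its metabolite are cleared mainly by the kidney, and that glomerular changes were seen in monkeys. Whether RO5024048 continues after a confirmed fall in creatinine clearance that is judged unrelated should not depend on which page a site reads. Cytopenias are also foreseeable, since section 5.1 names neutropenia as a significant boceprevir adverse event. Finally, SVR-12 is timed from the actual end of treatment (section 6.4.1), so sites that apply different rules could also start that clock differently for the same laboratory value.

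**Working it through.** No plan figure is in question, so the check is a comparison of the texts. The study drugs are RO5024048, boceprevir, Pegasys and Copegus. RO5024048 is given for at most 24 weeks, so a stop of RO5024048 alone can arise only while it is being taken.

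| Situation | Section 4.6.1.1 | Appendix F, RO5024048 rule |
|---|---|---|
| Confirmed, clinically significant Grade 4 value, related | Stop all drugs | Stop RO5024048 at once and call the Medical Monitor; silent on the other three |
| Same, unrelated | Stop all drugs | Not triggered; silent |
| Confirmed creatinine clearance fall ≥ 35% or < 60 mL/min, related | Stop RO5024048 | Stop RO5024048 at once and call the Medical Monitor |
| Same, unrelated | Stop RO5024048 | Not triggered; silent |

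**Step 1: does following one text satisfy the other?** A site that follows 4.6.1.1, and adds the immediacy and the call for related events, breaches nothing in Appendix F. The reverse fails in three of the four rows: a related Grade 4 value (three drugs continue), an unrelated Grade 4 value (all may continue), and an unrelated creatinine clearance fall (RO5024048 may continue). Only the related creatinine clearance row agrees on what is stopped.

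**Step 2: is there a sentence that sets precedence?** None was found in 4.6.1.1, Appendix F or Appendix G. Section 4.6.1.1 says should where Appendix F says must, so the wording does not make the main section clearly superior. The closing words of "Any clinically significant Grade 4 laboratory abnormality confirmed by repeat test, preferably within 1 week, unless otherwise defined" may exempt other defined cases or may only qualify the timing of the repeat test. Section 4.6.1.1 has no matching words.

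**Step 3: what do the other renal rules do?** Section 4.6.1.1 and Table H1 in Appendix H both stop RO5024048 for a confirmed urine protein/creatinine ratio of at least 0.5 that exceeds baseline, with no relatedness test. Appendix G schedules weekly monitoring for clearance of 60 to below 70 mL/min, or a fall of 25% to below 35%, also without one. The causality condition on the creatinine clearance stop is thus out of line with its neighbours.

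**Step 4: Table F3.** ANC < 500 in Table F3 equals Grade 4 in Appendix I, and platelets < 25,000 equals Grade 4. The next rows up (ANC < 750, platelets < 50,000) begin in Grade 3 and raise no conflict there. For the two lowest rows, an unconfirmed or non-significant count falls outside the 4.6.1.1 trigger, so Table F3 applies alone. A confirmed count that the investigator deems clinically significant meets both texts: stop all drugs, or hold (and, for ANC, restart Pegasys at 90 µg). The two differ in substance, because section 4.5.2.3 requires all study medication to end once Pegasys is stopped, whereas Table F3 foresees a return to it.

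**The case against.** The best defence is that the two texts form a general rule and a stricter subset rule. Section 4.6.1.1 sets the stop for any cause, and Appendix F escalates related cases with immediate action and a 24-hour call. Appendix F sits in a drug-by-drug appendix and never says that the other drugs, or RO5024048 after an unrelated event, should continue. Much of this stands. A reader might infer that the Appendix F Grade 4 item can never operate, or that it orders no drug to be stopped when the event is unrelated. The documents support neither inference: the item adds duties for related events, and its silence on unrelated events is not an instruction to continue. What the defence does not answer is that sites are sent to Appendix F for detail on stopping, and there find a condition that 4.6.1.1 lacks.

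On Table F3, the clinical significance test in 4.6.1.1 already separates most cases, so a reading that every Grade 4 count is in conflict would go too far. The boceprevir package insert, which Appendix G also cites for neutropenia, is not available here, so the full neutropenia instruction cannot be judged.

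Investigators may also stop any drug at any time (section 4.6.1), consult the sponsor in circumstances not listed (4.5.2.3), and must call the Medical Monitor over the renal findings in Appendix G. These routes reduce the risk, but they do not say which written action is intended. The background is also reassuring: section 1.2.1 reports no clinical renal injury with up to 24 weeks of RO5024048, and no increase in Grade 3 or 4 cytopenias in the Phase II studies.

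**Conclusion.** The point holds as a conflict between stated safety rules, not as a missing detail. For the same confirmed trigger, 4.6.1.1 acts whatever the cause, while Appendix F acts on RO5024048 only and only if the event is related. The most important consequence is that a patient could remain on a renally cleared drug after a confirmed creatinine clearance fall judged unrelated. The Table F3 overlap is real but narrow, limited to confirmed ANC < 500 or platelets < 25,000 that the investigator deems clinically significant.

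The conclusion assumes that some sites would read Appendix F as the operative rule, which the cross-reference makes plausible but does not prove. A reader might infer a bias in SVR-12. The protocol gives no rate for these events and no basis for how outcomes would change, both groups have the same regimen to Week 24, and the primary analysis is descriptive. No size can be put on such an effect. The texts should be aligned; nothing here undermines the design or the primary analysis.

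**What to change.** Align Appendix F to section 4.6.1.1, which is the more protective text, with three edits:

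1. In the Appendix F list for RO5024048, remove the relatedness condition from the creatinine clearance stop, and keep the Medical Monitor contact within 24 hours.
2. In the same list, state that a confirmed, clinically significant Grade 4 laboratory abnormality stops all study medications under 4.6.1.1, whatever the cause.
3. In Table F3, at the ANC < 500 and platelets < 25,000 rows, state that the row applies to counts not deemed clinically significant and that 4.6.1.1 governs otherwise. Because 4.6.1.1 also requires confirmation, Table F3 remains the action until the repeat result is in. The sponsor should check this sentence against the boceprevir package insert.

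The cost is a protocol amendment, with IRB/EC approval and, as locally required, authority approval (section 9.4); it can be bundled with the next one. No visit or test is added. There may be a few more discontinuations at sites that would otherwise have followed Appendix F.

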#### **4.6.1.2 Withdrawal from Study**

Every effort should be made to obtain information on patients who withdraw from the study. The primary reason for withdrawal from the study should be documented on the appropriate eCRF. Patients will not be followed for any reason after consent has been withdrawn. Patients who withdraw from the study will not be replaced.

#### **4.6.2 Study and Site Discontinuation**

The Sponsor has the right to terminate this study at any time. Reasons for terminating the study may include, but are not limited to, the following:

- The incidence or severity of AEs in this or other studies indicates a potential health hazard to patients.
- Previously unknown data become available that raise significant concerns about the potential risk from participation in the study.
- Patient enrollment is unsatisfactory.

The Sponsor will notify the investigator if the study is placed on hold or if the Sponsor decides to discontinue the study or development program.

The Sponsor has the right to replace a site at any time. Reasons for replacing a site may include, but are not limited to, the following:

- Excessively slow recruitment
- Poor protocol adherence
- Inaccurate or incomplete data recording
- Non-compliance with the International Conference on Harmonisation (ICH) guideline for Good Clinical Practice

## **5. ASSESSMENT OF SAFETY**

### **5.1 SAFETY PLAN**

Adverse events found during nonclinical studies of RO5024048 include glomerular microangiopathy with or without secondary hypertrophic/dilatory changes in the heart and a decrease in red blood cell parameters. A potential class effect of nucleoside analogs is mitochondrial toxicity.

Clinical trials have identified anemia and neutropenia as significant AEs associated with boceprevir (Victrelis USPI 2011). Pegasys/Copegus are associated with well-documented AEs such as psychiatric events; teratogenicity (with Copegus); cytopenias (including hemolytic anemia); flu-like symptoms; infections; and cardiovascular, thyroid, metabolic, autoimmune, respiratory, ophthalmic, and other conditions (Pegasys/Copegus USPI 2011).

Exclusion criteria in this study aim to exclude patients who are at risk for increased toxicity—as determined by the potential and identified AEs of RO5024048, boceprevir, and Pegasys/Copegus—such as patients with significant renal impairment, significant anemia, severe psychiatric disease, etc.

#### **5.1.1 Management of Specific AEs**

Regular monitoring of AEs, laboratory parameters, vital signs, and ECGs will ensure that any AEs (e.g., cytopenias) are detected early and treated promptly. Algorithms for the management of specific AEs/laboratory abnormalities (e.g., anemia, renal parameters) are provided in [Appendix G](#) and in the boceprevir, Pegasys, and Copegus package inserts (see [Appendix E](#)).

Dose-modification rules for this study are outlined in [Appendix F](#). The IMC will review the clinical trial data at regular intervals and at prespecified interim analyses.

## **5.2 SAFETY PARAMETERS AND DEFINITIONS**

Safety assessments will consist of monitoring and recording AEs, including SAEs and non-serious adverse events of special interest; measurement of protocol-specified safety laboratory assessments; measurement of protocol-specified vital signs; and other protocol-specified tests that are deemed critical to the safety evaluation of the study.

Certain types of events require immediate reporting to the Sponsor, as outlined in Section 5.4.

### **5.2.1 Adverse Events**

According to the ICH guideline for Good Clinical Practice, an AE is any untoward medical occurrence in a clinical investigation patient given a pharmaceutical product, regardless of causal attribution. An AE can therefore be any of the following:

- Any unfavorable and unintended sign (including an abnormal laboratory finding), symptom, or disease temporally associated with the use of a medicinal product, whether or not considered related to the medicinal product
- Any new disease or exacerbation of an existing disease (a worsening in the character, frequency, or severity of a known condition)
- Recurrence of an intermittent medical condition (e.g., headache) not present at baseline
- Any deterioration in a laboratory value or other clinical test (e.g., ECG, X-ray) that is associated with symptoms or leads to a change in study treatment or concomitant treatment or discontinuation from study drug
- Adverse events that are related to a protocol-mandated intervention, including those that occur prior to assignment of study treatment (e.g., screening invasive procedures such as biopsies)

### **5.2.2 Serious Adverse Events (Immediately Reportable to Roche)**

An SAE is any AE that meets any of the following criteria:

- Fatal (i.e., the AE actually causes or leads to death)
- Life threatening (i.e., the AE, in the view of the investigator, places the patient at immediate risk of death). This does not include any AE that had it occurred in a more severe form or was allowed to continue might have caused death.
- Requires or prolongs inpatient hospitalization (see Section 5.3.5.10)
- Results in persistent or significant disability/incapacity (i.e., the AE results in substantial disruption of the patient's ability to conduct normal life functions)
- Congenital anomaly/birth defect in a neonate/infant born to a mother exposed to study drug
- Significant medical event in the investigator's judgment (e.g., may jeopardize the patient or may require medical/surgical intervention to prevent one of the outcomes listed above)

The terms “severe” and “serious” are not synonymous. Severity refers to the intensity of an AE (rated as mild, moderate, or severe, or according to ACTG criteria; see Section 5.3.3); the event itself may be of relatively minor medical significance (such as severe headache without any further findings).

Severity and seriousness need to be independently assessed for each AE recorded on the eCRF.

Serious adverse events must be reported by the investigator to the Sponsor immediately (i.e., no more than 24 hours) after learning of the event (see Section 5.4.2 for reporting instructions).

### **5.3 METHODS AND TIMING FOR CAPTURING AND ASSESSING SAFETY PARAMETERS**

The investigator is responsible for ensuring that all AEs (see Section 5.2.1 for definition) are recorded on the AE eCRF and reported to the Sponsor in accordance with instructions provided in this section and in Section 5.4 – 5.6.

For each AE recorded on the AE eCRF, the investigator will make an assessment of seriousness (see Section 5.2.2 for seriousness criteria), severity (see Section 5.3.3), and causality (see Section 5.3.4).

#### **5.3.1 Adverse Event Reporting Period**

Investigators will seek information on AEs at each patient contact. All AEs, whether reported by the patient or noted by study personnel, will be recorded in the patient’s medical record and on the AE eCRF.

**After informed consent** has been obtained **but prior to initiation of study drug**, only SAEs caused by a protocol-mandated intervention should be reported (e.g., SAEs related to invasive procedures such as biopsies).

**After initiation of study drug**, all AEs, regardless of relationship to study drug, will be reported after the last dose of study drug according to [Appendix A](#). After this period, investigators should report any deaths, SAEs, or other AEs of concern that are believed to be related to prior treatment with study drug (see Section 5.6).

#### **5.3.2 Eliciting AE Information**

A consistent methodology of non-directive questioning should be adopted for eliciting AE information at all patient evaluation timepoints. Examples of non-directive questions include the following:

“How have you felt since your last clinic visit?”

“Have you had any new or changed health problems since you were last here?”

### 5.3.3 Assessment of Severity of AEs

Table 2 provides guidance for assessing AE severity.

**Table 2 AE Severity Grading Scale**

| Grade | Severity                                                                  | Alternate Description a                                                                                                                                              |
|-------|---------------------------------------------------------------------------|---------------------------------------------------------------------------------------------------------------------------------------------------------------------------------|
| 1     | Mild (apply event-specific ACTG grading criteria)                         | Symptoms causing no or minimal interference with usual social and functional activities                                                                                         |
| 2     | Moderate (apply event-specific ACTG grading criteria)                     | Symptoms causing greater than minimal interference with usual social and functional activities                                                                                  |
| 3     | Severe (apply event-specific ACTG grading criteria)                       | Symptoms causing inability to perform usual social and functional activities                                                                                                    |
| 4     | Potentially life threatening (apply event-specific ACTG grading criteria) | Symptoms causing inability to perform basic self-care functions OR medical or operative intervention indicated to prevent permanent impairment, persistent disability, or death |

ACTG = The Division of AIDS Table for Grading the Severity of Adult and Pediatric Adverse Events; AE, adverse event.

Note: Regardless of severity, some events may also meet regulatory serious criteria. Refer to definitions of a serious adverse event (see Section 5.2.2).

a Use these alternate definitions for Grades 1, 2, 3, and 4 events when the observed or reported AE is in the ACTG listing. ACTG v1.0 can be found in [Appendix I](#).

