### **Safety Outcome Measures**

- Incidence and severity of adverse events (AEs) and serious adverse events (SAEs) and reasons for discontinuation of any study medication. The Division of AIDS Table for Grading the Severity of Adult and Pediatric Adverse Events (ACTG) will be used to grade AEs.
- Clinically significant changes in vital signs, laboratory tests, and ECG results from screening/baseline

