### General Instructions

#### Estimating Severity Grade

If the need arises to grade a clinical AE that is not identified in the DAIDS AE grading table, use the category "Estimating Severity Grade" located at the top of Page 3. For AEs that are not listed in the table but will be collected systematically for a study/trial, protocol teams are highly encouraged to define study-specific severity scales within the protocol or an appendix to the protocol. (Please see "Template Wording for the Expedited Adverse Event Reporting Section of DAIDS-sponsored Protocols".) This is particularly important for laboratory values because the "Estimating Severity Grade" category only applies to clinical symptoms.

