| ESTIMATING SEVERITY GRADE                                                                                                                                            |                                                                                       |                                                                                                                   |                                                                                                          |                                                                                                                                                                                 |
| Clinical adverse event NOT identified elsewhere in this DAIDS AE grading table                                                                                              | Symptoms causing no or minimal interference with usual social & functional activities | Symptoms causing greater than minimal interference with usual social & functional activities                      | Symptoms causing inability to perform usual social & functional activities                               | Symptoms causing inability to perform basic self-care functions OR Medical or operative intervention indicated to prevent permanent impairment, persistent disability, or death |
| SYSTEMIC                                                                                                                                                             |                                                                                       |                                                                                                                   |                                                                                                          |                                                                                                                                                                                 |

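### Footnote a of Table 2 (Section 5.3.3) states the AE grading rule backwards, so it conflicts with the table's own Severity column and with Appendix I

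*Protocol*

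**What the plan says.** Section 5.3.3 refers investigators to Table 2 for assessing AE severity. At each of the four grades the Severity column sends the reader to the event-specific criteria; the Grade 1 cell reads "Mild (apply event-specific ACTG grading criteria". A further column gives a generic alternate description, and footnote a says when to use it: "Use these alternate definitions for Grades 1, 2, 3, and 4 events when the observed or reported AE is in the ACTG listing". The same footnote refers the reader to Appendix I for the listing.

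Appendix I reproduces the DAIDS table. Its general instructions say: "If the need arises to grade a clinical AE that is not identified in the DAIDS AE grading table, use the category" named Estimating Severity Grade. They add that this "category only applies to clinical symptoms", a point made with laboratory values in mind. The row of the table that holds the generic wording is labelled "Clinical adverse event NOT identified elsewhere in this DAIDS AE grading table".

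The Synopsis, under Safety Outcome Measures, names the instrument: "The Division of AIDS Table for Grading the Severity of Adult and Pediatric Adverse Events (ACTG) will be used to grade AEs". Section 3.4.2 says the same in substance.

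**The concern.** The footnote assigns the generic descriptions to the events for which specific criteria exist. That looks like a dropped *not*, but it sits in the section from which investigators grade events at the site. It is not something that an analysis plan can repair later, because the grade is already in the eCRF by then.

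Incidence and severity of AEs is a named safety outcome, and comparing safety and tolerability between the groups is a secondary objective (Section 2.2). Section 5.1 expects anemia, neutropenia and other cytopenias with this combination. These are events for which Appendix I grades by a measured value and the generic wording grades by symptoms. With about 60 patients at 35 to 40 sites, a site contributes on average 60/40 = 1.5 to 60/35 = 1.7 patients, so differences between sites in how the footnote is read would bear directly on the small severity tables.

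**Working it through.** The protocol states no figure on this point, so the check is to set the texts side by side and grade example events under both readings.

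**Step 1. Which rule applies to which event?**

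| Source | Listed event | Unlisted clinical event | Laboratory value |
|---|---|---|---|
| Table 2, Severity column | Event-specific criteria | No such criteria exist | Event-specific criteria |
| Table 2, footnote a | Generic description | Not addressed | Generic description, since laboratory tests are in the listing |
| Appendix I | Event-specific criteria | Generic description | Numeric limits; generic category excluded |

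The footnote disagrees with Appendix I in the first and third columns and is silent in the second. It also contradicts the Severity column of its own table. The wording of Appendix I's generic row matches Table 2's alternate column, so both describe the same scale. Only the condition for its use differs.

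**Step 2. Do such events become AEs that are graded?** Section 5.3.5.4 makes a laboratory result an AE if, among other criteria, it leads to a change in study treatment. Section 5.3 requires a severity for each recorded AE. An ANC of 600/mm3 falls in a row of Table F3 and a hemoglobin of 8.0 g/dL falls within Table F4. Where treatment is changed on that account, the result must be recorded and graded as an AE.

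**Step 3. Grades under the two readings.** Anti-HIV-positive patients are excluded (Section 4.1.2, criterion 3), so the HIV-negative hemoglobin limits apply. The generic column assumes a patient without symptoms, for whom no intervention is judged necessary to prevent permanent impairment, persistent disability or death.

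| Reported AE | Appendix I | Generic wording | Difference |
|---|---|---|---|
| Hemoglobin 8.0 g/dL (band 7.0–8.9) | 3 | 1 | 3 − 1 = 2 |
| ANC 600/mm3 (band 500–749) | 3 | 1 | 3 − 1 = 2 |
| QTc 0.50 s or more | 3 | 1 | 3 − 1 = 2 |
| Hemoglobin 6.8 g/dL (below 7.0) | 4 | 1 | 4 − 1 = 3 |
| ANC 400/mm3 (below 500) | 4 | 1 | 4 − 1 = 3 |

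**Step 4. Is the direction uniform?** No. Headache and fatigue at Grades 1 to 3 already carry the generic wording in Appendix I, so their grades there do not move. Deep vein thrombosis with intervention indicated is Grade 3 in the listing. The second part of generic Grade 4, which turns on intervention to avert lasting harm or death, could place it at Grade 4. The same part could keep an ANC of 400/mm3 at Grade 4.

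**The case against.** The strongest reply is that one footnote, plainly missing a word, stands against all four Severity cells, the outcome definition and the full grading table in Appendix I. A careful investigator would notice and follow the listing. The generic descriptions for Grades 1 to 3 speak of symptoms and do not naturally fit an asymptomatic laboratory value. Much of the safety reporting is also insulated. Section 6.5 analyses laboratory data under the sponsor's own guideline, and Tables F3 and F4 work from numeric limits whatever grade is recorded.

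Most of this stands, and it limits the consequence. Under-grading is not certain; what is certain is that the instructions conflict. It does not rescue the footnote, because no reading makes it agree with Appendix I, and the separate laboratory summaries do not protect the AE severity tables.

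Three stronger inferences are tempting, and the protocol does not support them:

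- A reader might infer that unlisted events are left with no scale. Appendix I supplies one, and the footnote itself points there.
- A reader might infer that all listed and laboratory events would be under-graded. Step 4 shows that some are unchanged and some could rise.
- A reader might infer that the stopping rule in Section 4.6.1.1, "Any confirmed Grade 4 laboratory abnormality deemed clinically significant", would misfire. That rule refers to a laboratory abnormality, for which grades are defined only in Appendix I's laboratory section. It also requires the investigator's judgement of clinical significance. Its natural reading does not pass through the AE footnote.

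**Conclusion.** The point holds as an inverted instruction in Section 5.3.3. Footnote a contradicts both its own table and Appendix I, and a site that obeys it would mis-grade listed AEs. The error is mainly under-grading of asymptomatic events defined by objective limits: two grades for hemoglobin 8.0 g/dL or ANC 600/mm3, and three grades at worst, for values in the Grade 4 bands. These sizes assume no symptoms and no intervention judged necessary to prevent lasting harm or death.

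The damage is confined to AE severity as recorded by investigators and to the tables built on it. The protocol gives no evidence that any site followed the footnote, so it does not support calling those tables uninterpretable. The risk is inconsistent grading of a named safety outcome in a small trial spread over many sites.

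**What to change.** Reconcile footnote a with Appendix I so that the alternate descriptions apply when the event *is not in the ACTG listing*. Add one sentence stating that laboratory abnormalities reported as AEs are graded by the laboratory limits in Appendix I. Notify the sites of the correction, and query grades already entered for listed terms, starting with cytopenias and other events graded on a measured value.

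The text change is one word and one sentence in an amendment. The remaining cost is a site notice and a targeted data query in a trial of about 60 patients. No endpoint, sample size or analysis method changes.
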